#### Measures for sample size estimation

Clinical outcomes measures. In line with DSM V criteria for AN and OSFED-AN type (atypical AN) which emphasises rate of weight loss and ED cognitions, the primary outcome measure is of eating disorder cognitions and behaviours for sample size estimation—Eating Disorder Examination Questionnaire (EDEQ).^25^ Other indications of symptoms, such as BMI (kg/m^2^); Depression, Anxiety and Stress Scales 21^26^ and Clinical Impairment Assessment^27^ are also collected.

Intervention-specific measures. Other clinical and Intervention-specific measures will also be assessed as follows: Beliefs About Emotions Questionnaire,^28^ Young’s Schema Questionnaire–Short Form (SF),^29^ Schema Mode Inventory ED–SF (SMI-ED-SF)^30^; Silencing the Self Scale,^31^ The Sense of Agency Scale^32^ and Difficulties with Emotion Regulation Scale.^33^

#### Measures of economic evaluation

An adapted version of the Client Sociodemographic and Services Receipt Inventory^34^ will collect economic data preintervention and postintervention to assess treatment costs received in the 6 months preceding and during SPEAKS.

#### Measures of SPEAKS Change Process

The following analyses will test hypothesised therapeutic change process.

Videoed therapy sessions will be analysed according to two coding systems to better understand change associated with better clinical outcomes, including hypotheses about both content and order of change. The Innovative Moments Coding System^35^ is a systematic reliable method for identifying innovative moments (IMs) in therapy, categorising by type (action, reflection, protest, reconceptualisation, performing change). IMs are measured by the percentage of time spent elaborating on each IM (temporal salience). The Classification of Affective Meaning States (CAMS)^36^ codes the presence of emotions expressed during therapy videos in) 1 min segments. The CAMS includes nine emotion categories: global distress (rejecting anger, fear/shame, negative self-evaluation, unmet need, relief, assertive anger/self-compassion, hurt/grief, and acceptance/agency) which will be analysed to assess changes in patterns of emotion expression over time including emotion types and frequency.^37^Thematic analysis will be applied to psychological formulations of ‘schema modes’ constructed by participants during therapy as compared against those endorsed in a quantitative measure (SMI-ED^30^). This will enable us to improve the SPEAKS intervention based on the most salient schema modes, and mode changes associated with better outcomes.

Participants may participate without agreeing to their formulations or therapy recordings being analysed.

### Participant timeline

Participants will be assessed using quantitative variables examining clinical and emotion change collected preintervention, at 3, 6 and 9 months into the intervention and postintervention (12 months; figures 3 and 4). Collecting questionnaire data every 3 months is standard practice within the EDS. Due to the coronavirus pandemic, some participants experienced a break in their SPEAKS therapy. In order to ensure that all participants are able to access the full 9–12 months of therapy intended, therapy will be extended for those impacted by a maximum of 3 months. Where relevant, this will be discussed and agreed between therapist and participant. In order to capture end of therapy data for those affected, we will include an extra data collection time point at 15 months just for these participants. The 15 months data collection point will be considered equivalent to the 12 months time point of unaffected participants, with other assessment time points adjusted accordingly to ensure progress is captured every 3 months within therapy.

**Figure 3 F3:**
[figure not shown]
SPEAKS spirit schedule. CSSRI, Client Socio-demographic and Services Receipt Inventory; SPEAKS, Specialist Psychotherapy with Emotion for Anorexia in Kent and Sussex.

### Sample size

The feasibility design must balance precision with unethical exposure of participants to the risks being monitored alongside unnecessary expense.^38^ Teare *et al*^39^ recommend 35 participants for sufficient feasibility data and precision of mean and variance. Therapy attrition rates for people with AN can reach 40%.^9^ With a sample size of 36, we will be able to estimate a drop-out rate of 40% to within a 95% CI of ±16%. These data suggest an approximate revised sample size of up to 60 participants in order to achieve a sample of 36 participants completing therapy.

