**Methods and analysis:**

This study employs a multisite, single-arm, within-group, mixed-methods design. Up to 60 participants (36 therapy completers) meeting inclusion criteria will be offered the SPEAKS intervention instead of treatment-as-usual (TAU). SPEAKS is a weekly psychotherapy lasting nine to 12 months, provided by trained and experienced eating disorders therapists. All other clinical input remains inline with TAU. Acceptability will be assessed using VAS scales and end of therapy interview. Reach and recruitment, such as recruitment yield, will be monitored. To support sample size estimation and economic estimation, data pertaining to eating disorder-related symptoms will be recorded every 3 months, alongside service usage and intervention-specific measures. Videoed therapy sessions will inform model adherence. Additional analyses coding videoed therapy will test SPEAKS change process hypotheses.

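### The ±16% drop-out precision is computed on 36, the expected number of completers; on the up to 60 who start it is about ±12 percentage points

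*Protocol article*

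**What the plan says.** The Sample size section gives 36 two roles in consecutive sentences.

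- It first notes that "Therapy attrition rates for people with AN can reach 40" per cent, and then gives the precision: "With a sample size of 36, we will be able to estimate a drop-out rate of 40% to within a 95% CI of ±16" per cent. Here 36 is the sample in which drop-out is estimated.
- It then draws the enrolment figure: "These data suggest an approximate revised sample size of up to 60 participants", which is needed "in order to achieve a sample of 36 participants completing therapy". Here 36 is the number left once drop-out has happened.

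The abstract, under Methods and analysis, agrees with the second role: "Up to 60 participants (36 therapy completers) meeting inclusion criteria will be offered the SPEAKS intervention". The Sample size section also cites a recommendation of 35 participants for the precision of the mean and variance, and 36 fits that purpose. The article gives no drop-out precision for 60, and nowhere describes a starting cohort of 36.

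**The concern.** A drop-out rate is the number who leave divided by the number who start. If 36 people are the completers, none of them has dropped out, so they cannot form the denominator of that rate. Two sample sizes with different jobs appear to have been merged: the people who start, who determine the precision of the drop-out rate, and the people who finish, who determine the precision of the outcome mean and standard deviation.

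This is the only numerical precision that the article gives for any feasibility quantity. Drop-out is also one of the problems that motivates the trial: the Introduction and the Challenges section both describe it as high in this population. A reader who relies on the sentence would take the planned trial to be less informative about drop-out than it is.

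**Working it through.** **Inputs, all from the Sample size section:** drop-out proportion p = 0.40; 95% confidence, two-sided, so z = 1.96; 36 completers; up to 60 participants.

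**Step 1. Reproduce the plan's figure.** The normal-approximation half-width is z × √(p(1 − p)/n). With n = 36:

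1.96 × √(0.40 × 0.60 / 36) = 1.96 × 0.08165 = 0.160, or ±16 percentage points.

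Solving the formula for n at a half-width of 0.16 gives 0.24 × (1.96/0.16)² ≈ 36.0, so 36 was the denominator used. Other methods at n = 36 fit less well: continuity-corrected ±17.4, Wilson ±15.2, and exact about ±16.7 (for 14 of 36, the nearest whole count).

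**Step 2. Establish what 36 is.** 36 / (1 − 0.40) = 60, and 60 × 0.60 = 36. The same 40% attrition has already been taken off to reach 36, which leaves 60 × 0.40 = 24 expected drop-outs outside that group.

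**Step 3. Recompute on those who start.** The same formula with p = 0.40:

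| Number starting | 95% half-width (percentage points) |
|---|---|
| 60 | 1.96 × √(0.24/60) = 12.4 |
| 55 | 12.9 |
| 50 | 13.6 |
| 40 | 15.2 |
| 36 | 16.0 |

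The range is shown because 60 is a ceiling. At 60, the normal approximation gives 27.6% to 52.4%, Wilson 28.6% to 52.6%, and the exact interval for 24 of 60 is 27.6% to 53.5%. The choice of method moves the limits by about one point and does not alter the conclusion.

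**Step 4. Size of the discrepancy.** 16.0 / 12.4 = 1.29, so the stated half-width is about 29% wider than the one that 60 starters give.

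**The case against.** The best defence is that the sentence is conditional on a sample of 36, and for that sample the arithmetic is right. The article never claims that ±16 applies to 60. Calling 60 a revised figure may mean that 36 was once the planned starting number, although that is inference. The stated figure is also safe: at 40% drop-out, any enrolment from 36 to 60 gives ±16 or tighter. The enrolment figure does not depend on it, and recruitment has already ended.

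Much of this stands. There is no slip in the calculation, the error is in the cautious direction, and the design does not change. The conditional wording does not rescue the sentence, though. The plan contains no starting group of 36, and the next sentence uses that number for completers.

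A reader might infer more than the document supports:

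- *That retention decides progression to a larger trial.* No such rule is set. The progression hypothesis under Objectives concerns reach and recruitment, and Potential implications says only that the study will inform whether larger trials are appropriate.
- *That the wrong figure feeds into the size of the next trial.* Data analysis bases that calculation on EDEQ change and mentions no inflation for drop-out.
- *That drop-out will actually be calculated among completers.* Nothing says so, and the result would be zero by definition. The article plans to count people who end therapy because they find it unacceptable, and to report removals from the trial.
- *That 36 completers are at risk because drop-out may exceed 40%.* The article gives 40% as a level that attrition can reach and offers no higher scenario.

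**Conclusion.** The point holds as a minor error of denominator. The drop-out precision is stated on the expected completers and should be stated on those who start: about ±12 percentage points at 60, ±14 at 50 and ±15 at 40, in place of ±16. The target of 60 follows correctly from 36/0.60 and stands.

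This rests on three assumptions: drop-out is exactly 40%, as the plan supposes; participants drop out independently, with no allowance for site or therapist; and the up to 60 participants are those who start therapy. The article does not separate enrolling from starting. If some enrol and never start, the relevant row of the table is the one for the smaller number.

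**What to change.** Replace the precision sentence in the Sample size section with wording such as: *With 60 participants starting SPEAKS, a drop-out rate of 40% will be estimated to within ±12 percentage points (95% CI), or ±15 if only 40 start, with all participants who start therapy as denominator.* Follow it with a sentence saying that the 36 expected completers are the sample for the precision of the outcome mean and variance.

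This costs one edit. It needs no extra participants and changes neither the enrolment target nor any planned analysis. It is still useful after the close of recruitment, because the drop-out rate has yet to be reported and its denominator would then be stated in advance.

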### Recruitment

Patients will be consecutive referrals meeting inclusion/exclusion criteria to the two sites in South-East England: North East London NHS Foundation Trust (NELFT) and Sussex Partnership NHS Foundation Trust (SPFT). Participants will be identified from waiting lists in the first instance in order of referral. Recruitment will continue until SPEAKS therapists no longer have available spaces and will recommence when further spaces come available. Recruitment ended in February 2021. This was after journal submission, but prior to completion of peer reviews.

## Methods: data collection, management and analysis

### Allocation, allocation concealment and blinding

Not applicable due to the single arm design.

### Data collection methods and retention

Informed consent and data at all time-points will be organised and collected by a research assistant specifically employed to complete this role. Mutually agreed appointment times for completion of all measures will be agreed. The research assistant will maintain engagement of participants with regular newsletters and individual correspondence.

### Data management and availability

Data entry errors will be checked by double entering 10% of data. Examining data for impossible values by looking at data ranges will test data quality. No post-treatment data will be released until the database is locked. Access to the final trial dataset will be available to the PIs and research assistant. The datasets generated and/or analysed during the current study will be included in the subsequent results publication. Anonymised participant-level data available on request.

### Data analysis

The data will be analysed using password protected NHS computers at NELFT. It will be analysed by PIs, the research worker and clinical psychology trainees as part of their doctoral theses. Thematic analysis of acceptability interviews will be completed before quantitative analysis of acceptability data to avoid bias. Dependent t-tests (or non-parametric equivalents) and effect sizes (Cohen’s d) will be calculated for all outcomes measures. EDEQ change will be used in a power analysis to estimate sample size required for effectiveness trial. We will model for missing data of anybody who completed therapy.

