### Interventions

#### Speaks intervention

SPEAKS is an individual outpatient psychotherapy for adults with AN. Participants receive weekly individual sessions of psychotherapy for 9–12 months with two follow-up sessions within 3 months of completion. SPEAKS is intended to be offered face to face in a clinic setting; however, due to the COVID-19 pandemic video sessions via on an online platform are provided.

SPEAKS is a direct replacement for psychotherapy as usual. Therapists receive fortnightly supervision by supervisors trained in the supervision requirements of SPEAKS. The services at both sites are in the same region of the UK and follow national NHS treatment guidelines. All usual care procedures, including additional interventions such as dietician appointments or inpatient referrals will remain the same, but be reported. People will be removed from the trial if they require immediate inpatient treatment at any point or request removal for any reason, and these data will be reported.

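### The paired t-tests leave interim waves, drop-outs' partial data and therapist clustering out of the EDEQ change that is meant to size the next trial

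*Protocol article*

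**What the plan says.** Protocol article, Data analysis: "Dependent t-tests (or non-parametric equivalents) and effect sizes", the latter as Cohen's d, are planned for every outcome measure. The section does not say which time points are compared and mentions neither therapist nor site. It continues: "EDEQ change will be used in a power analysis to estimate sample size required for effectiveness trial". On missing data it says: "We will model for missing data of anybody who completed therapy".

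Protocol article, Participant timeline: measures are taken before therapy, at 3, 6 and 9 months, and at 12 months as the post-intervention point. For participants whose therapy was broken by the pandemic, "therapy will be extended for those impacted by a maximum of 3 months", and "The 15 months data collection point will be considered equivalent to the 12 months time point of unaffected participants". Their other waves are shifted to stay three-monthly within therapy.

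Protocol article, Sample size: attrition may reach 40%, and up to 60 people are enrolled so that 36 complete. The same section justifies the number by the precision of a mean and a variance.

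Protocol article, Participant timeline and Recruitment: therapists are interviewed after their last SPEAKS participant, and recruitment pauses when therapists have no space. A therapist therefore sees more than one participant. The article gives neither the number of therapists nor an intraclass correlation.

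**The concern.** Setting the parameters of a later trial is one of the stated objectives, and EDEQ change is the figure handed on for that purpose. It deserves the best use of the data, even though no hypothesis test is powered here.

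The named method falls short in three ways:

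- **Waves.** A paired comparison takes two scores per person. The 3-, 6- and 9-month scores do not inform the baseline-to-end estimate.
- **Drop-outs.** Someone who leaves after month 6 has three scores, none of which enters that estimate. The missing-data model does not reach them, because it is limited to completers.
- **Therapists.** The test assumes independent participants. If outcomes are alike within therapist, its standard error is too small.

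At stake are the precision of the EDEQ change, possible bias in it as an estimate for everyone who starts therapy, and how much confidence the next trial's planners place in it.

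**Working it through.** **1. The plan's own figures reproduce.** The half-width for 40% drop-out at n = 36 is 1.96 × √(0.40 × 0.60 / 36) = 0.160, which is the stated ±16%. Enrolment is 36 / (1 − 0.40) = 60. So up to 60 − 36 = 24 participants may not complete and would lie outside both the end-point comparison and the missing-data model.

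**2. Interim waves and drop-out.** This is a simulation, and all of its inputs except the 60 enrolled, the five waves and the 40% drop-out are assumptions. The mean path is 0, −0.25, −0.50, −0.70, −0.80 SD and the correlation between waves is 0.7^lag. The log-odds of leaving before the next wave rise by b per SD of the latest score. There were 2,000 repeats per row. The target is the mean change of everyone who starts, −0.80 SD.

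| b | Completers, paired change (SE) | All waves, likelihood estimate (SE) |
|---|---|---|
| 0 (random drop-out) | −0.804 (0.202) | −0.799 (0.183) |
| 0.5 | −0.746 (0.200) | −0.799 (0.189) |
| 1.0 | −0.686 (0.198) | −0.796 (0.195) |

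- Precision under random drop-out: (0.202 / 0.183)² = 1.22, so the paired estimate has about 22% more variance.
- Bias under outcome-dependent drop-out: 0.800 − 0.746 = 0.05 SD and 0.800 − 0.686 = 0.11 SD. In this scenario the change is understated. The direction depends on who leaves.
- Consequence, if the next trial's target effect were set in proportion to this change and its size went as 1/d²: (0.80 / 0.746)² = 1.15 and (0.80 / 0.686)² = 1.36, a trial 15% to 36% larger than needed.

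The all-wave column is an unrestricted multivariate normal likelihood estimate. A mixed model with a simpler covariance structure is of the same kind but need not match it exactly.

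**3. Therapist clustering.** Design effect = 1 + (m − 1) × ICC, with m = 36 / number of therapists. The true SE exceeds the paired-test SE by about √(design effect), and effective n = 36 / design effect. Therapist numbers and ICCs are assumptions.

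| Therapists (m) | ICC | Design effect | SE multiplier | Effective n |
|---|---|---|---|---|
| 6 (6) | 0.01 | 1.05 | 1.02 | 34.3 |
| 6 (6) | 0.05 | 1.25 | 1.12 | 28.8 |
| 6 (6) | 0.10 | 1.50 | 1.22 | 24.0 |
| 6 (6) | 0.20 | 2.00 | 1.41 | 18.0 |
| 12 (3) | 0.01 | 1.02 | 1.01 | 35.3 |
| 12 (3) | 0.05 | 1.10 | 1.05 | 32.7 |
| 12 (3) | 0.10 | 1.20 | 1.10 | 30.0 |
| 12 (3) | 0.20 | 1.40 | 1.18 | 25.7 |

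Over this range the true SE is 1% to 41% larger than reported. With clusters of similar size the mean change does not move, and Cohen's d shifts by at most about 1.5%.

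**4. The 15-month rule.** Shift in the mean = share affected × extra change over the added 3 months. With 10% to 50% affected and 0 to 0.2 SD extra (assumptions), it runs from 0 to 0.5 × 0.2 = 0.10 SD. The 95% CI half-width at n = 36 is 2.03 / √36 = 0.34 SD of change. If the quantity wanted is change to end of therapy, the shift is zero by definition.

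**The case against.** The strongest reply is that this is a single-arm feasibility study with no powered test and no efficacy hypothesis. The article condenses a fuller protocol, and it never says that only one pre-post comparison is made. Tests from baseline to each wave would fit its wording, and the missing-data model might draw on the interim scores. Part of this stands: the study is not invalidated, and the matter is one of improvement. But the article states a method rather than leaving one open. Separate paired tests at each wave still do not combine waves, do not bring drop-outs' scores into the end-point estimate and do not account for therapist. The missing-data model is expressly confined to completers.

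It may also be said that the bias needs outcome-dependent drop-out and a target of everyone who started. That is correct. If only completers are of interest, or drop-out is random, what remains is a loss of precision at most.

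Three stronger readings are tempting and are not supported:

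- **Pooling 15-month with 12-month scores inflates the change.** The rule is openly stated, limited to interrupted participants and aligned to end of therapy. Inflation follows only if change tracks calendar time, including time during the break. Since therapy may run for 9 to 12 months ("Participants receive weekly individual sessions of psychotherapy for 9–12 months with two follow-up sessions within 3 months of completion"), time since the last session does vary at month 12, but a fixed 12-month assessment would have the same feature.
- **Clustering biases the change.** It affects the standard error. The mean is unaffected when therapists see similar numbers.
- **Testing many scales will yield chance findings.** The Data analysis section sets no significance threshold, EDEQ is named as primary for sample size estimation, and the article declares the single-arm limitation itself.

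**Conclusion.** The point holds as a cheap improvement. The named paired tests, with missing data modelled only for completers, make weaker use of the data than the design allows. In the assumed scenario the EDEQ change has an SE of 0.20 rather than 0.18 under random drop-out, and a bias of about 0.05 to 0.11 SD if leaving depends on earlier scores and the target is everyone enrolled. Its standard error may also be too small: the true one is 1% to 41% larger for 6 to 12 therapists and ICCs of 0.01 to 0.20. The actual amount is unknown because the article gives neither quantity.

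A reader might infer that the change estimate is wrong. The document does not support that: bias depends on a drop-out pattern not yet known, clustering leaves the mean alone, and the 15-month rule is a legitimate definition of the end point.

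**What to change.** For EDEQ and the other repeatedly measured outcomes, fit a linear mixed model to all available waves from all enrolled participants. Include a participant random effect, site as a fixed effect, and either a therapist random effect or a sensitivity analysis for therapist. Report change from baseline to end of therapy (12 months, or 15 months for interrupted participants, as Participant timeline defines it) with a 95% CI. Add a sensitivity analysis that uses actual months since baseline. Carry a range of therapist ICCs into the sample size for the effectiveness trial.

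The cost is a change of wording and modest extra analysis on data already being collected. Intervals may become wider, and the therapist variance will be imprecise if therapists are few, which is why a range of ICCs is preferable to a single estimate. The model relies on drop-out being explained by the scores already observed. It does not remove bias from drop-out that depends on unobserved scores.

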## Abstract

**Introduction:**

Anorexia nervosa (AN) is a severe mental health condition associated with high mortality rates and significantly impaired quality of life. National guidelines outline psychotherapeutic interventions as treatments of choice for adults with AN, but outcomes are limited and therapy drop-out high, resulting in calls for new innovative treatments. The Specialist Psychotherapy with Emotion for Anorexia in Kent and Sussex (SPEAKS) research programme sought to develop the SPEAKS intervention avoiding some difficulties inherent in development of earlier interventions, such unclear hypotheses about change processes. SPEAKS focuses on a core hypothesised maintaining factor (emotional experience) with clear proposed model of change. The current feasibility trial aims to provide an initial test of SPEAKS and inform design of a full randomised controlled trial protocol.

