## Introduction

### Background and rationale

Anorexia nervosa (AN) is a severe mental illness with poor prognosis and the highest mortality rate of any psychiatric disorder.^1^ Early intervention is key, but is impeded by a delay of around 18 months from symptoms emerging to treatment, and with multiple relapses likely.^2^ Caregiving for somebody with severe AN is almost twice as lengthy as for somebody with a physical health disorder (eg, cancer) or other mental health difficulty (eg, psychosis).^3^ Thus significant costs exist financially and emotionally to the individual, family and carers, as well as society as a whole, offering a ‘compelling case for change’ in services and treatment (PricewaterhouseCoopers, p.9).^2^

Most recent NICE guidelines in the UK recommend that psychotherapeutic interventions be considered for adults with AN.^4^ Yet results from randomised controlled trials indicate that outpatient treatments do not out-perform each other or control comparisons^5–9^ with weight-restoration achieved by 20% of patients after 1 year.^7–9^ AN is highly valued by sufferers resulting in poor treatment engagement and high drop-out rates.^10^ Thus there is an urgent need to develop innovative interventions that can engage people with AN,^4 11 12^ while targeting unique factors involved in its development and maintenance.^13^ Emotional experience has long been recognised as a factor in the development and maintenance of AN and is recognised as a promising target area for therapies^14^ and increasingly incorporated into psychotherapy interventions for adults with AN.^5–9^ However, outcomes remain limited and it is unclear to what extent emotional difficulties are targeted by these interventions.^15^

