### Trial design

The SPEAKS study is a multisite, single-armed, within-group mixed-methods design.

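### The future trial's sample size is to rest on uncontrolled EDEQ change, which does not estimate the between-arm difference a randomised trial is powered on

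*Protocol article*

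**What the plan says.** The Trial design section states: "The SPEAKS study is a multisite, single-armed, within-group mixed-methods design". The abstract says the study is to "inform design of a full randomised controlled trial protocol". Under Measures for sample size estimation, the EDEQ is given its role: "the primary outcome measure is of eating disorder cognitions and behaviours for sample size estimation".

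The Data analysis section then sets out two steps in succession. First: "Dependent t-tests (or non-parametric equivalents) and effect sizes (Cohen’s d) will be calculated for all outcomes measures". Next: "EDEQ change will be used in a power analysis to estimate sample size required for effectiveness trial". The article gives no target between-group difference, no expected change in a control arm and no discount to the pre-to-post effect.

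The future comparator is not named. The intervention section says "SPEAKS is a direct replacement for psychotherapy as usual", which suggests an active comparator without fixing one. The strengths and limitations list concedes the single-arm design, but only for bias and for the acceptability of randomisation, not for sample size estimation.

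**The concern.** A two-arm trial is powered on the difference between the arms' mean outcomes. A single-arm study observes the change in one of those arms. The two coincide only if control patients do not change at all. Any improvement from natural course, regression to the mean or other care counts in full towards the pre-to-post change and cancels out of the between-arm difference.

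Sample size estimation is one of the study's stated objectives, and the EDEQ is designated primary for that purpose. If the observed mean change or the within-group Cohen's d is entered as the assumed effect, the study delivers a sample size for the wrong quantity. The error runs towards too small a trial whenever controls improve.

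**Working it through.** **The article's own figures.** No size for the future trial is stated, so there is none to reproduce. The figures under Sample size do reproduce: 1.96 × √(0.4 × 0.6 / 36) = 0.160, the stated ±16 points, and 36 / (1 − 0.40) = 60.

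**Inputs for the check.** All are assumptions, because the article gives none: two-sided α = 0.05, 80% power, equal allocation, outcome SD = 1, and a within-group d of 0.5 to 1.0 entered as if it were the between-group effect. Let s be the share of the same EDEQ change that control patients also show. The true between-group effect is then d × (1 − s).

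**Formulas** (normal approximation):
- n per arm = 2 × (1.960 + 0.842)² / d²
- power = Φ(d × (1 − s) × √(n/2) − 1.960)

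**Worked case, d = 0.8.** n = 2 × 7.849 / 0.64 = 24.5, so 25 per arm, and √(25/2) = 3.536.
- s = 0.25: effect 0.6; Φ(2.121 − 1.960) = 0.564; n needed 15.70 / 0.36, so 44
- s = 0.50: effect 0.4; Φ(1.414 − 1.960) = 0.293; n needed 15.70 / 0.16, so 99
- s = 0.75: effect 0.2; Φ(0.707 − 1.960) = 0.105; n needed 15.70 / 0.04, so 393

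**Other values of d.**

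| d assumed | n per arm as sized | Power at s = 25% / 50% / 75% | n per arm needed |
|---|---|---|---|
| 0.5 | 63 | 0.558 / 0.289 / 0.104 | 112 / 252 / 1005 |
| 0.8 | 25 | 0.564 / 0.293 / 0.105 | 44 / 99 / 393 |
| 1.0 | 16 | 0.564 / 0.293 / 0.105 | 28 / 63 / 252 |

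The power loss hardly depends on d. Sizing for 80% power fixes d × √(n/2) at about 2.80, so the true value is 2.80 × (1 − s) whatever d was. Required n rises by 1 / (1 − s)²: 1.8-fold, 4-fold and 16-fold. With s = 0, power stays at about 80%. Sizing d = 0.8 for 90% power (33 per arm) gives 0.683, 0.369 and 0.126 at the same three shares.

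**Precision of the SD.** At n = 36 the 95% confidence limits for an SD are √(35 / χ²) = 0.81 and 1.30 times the estimate. Required n scales with the SD squared, so this alone moves it by a factor of 0.66 to 1.70. The SD is a legitimate product of this study, but it should not be used as an exact value.

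**The case against.** The strongest reply is that the sentence does not say which quantity from EDEQ change enters the calculation. Change data also yield the SD of change and the baseline-to-post correlation, which are proper inputs. The Sample size section justifies the numbers by the precision of both mean and variance. If only the SD were used, with a separately justified target difference, the objection to the effect size would fall away. That reading is possible, but the text does not state it. The sentence follows directly on the calculation of Cohen's d, and no target difference appears anywhere. At the least it needs rewriting.

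A second reply is that the shortfall is hypothetical. This stands as to size. A reader might infer that the future trial is bound to be badly underpowered, but the documents do not support that: the effect sizes and control shares above are assumed, and with no control-arm change nothing is lost. The illustration also treats d as standardised by the outcome SD. A d divided by the SD of change would equal it only at a baseline-to-post correlation of 0.5, so the per-arm numbers are not what the plan itself would produce.

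A third reply concerns the background, which says "results from randomised controlled trials indicate that outpatient treatments do not out-perform each other or control comparisons". A reader might take this to show that most of the EDEQ change would also occur in a comparator. It reports no EDEQ change for any arm, so it makes control improvement plausible without measuring it. Likewise, psychotherapy as usual is a likely comparator, not a stated one.

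Finally, the step affects no participant and no acceptability, recruitment or adherence result here. That is true, and it is why the point can still be corrected. It does not make the stated basis sound.

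**Conclusion.** The point holds. As written, the article bases the future trial's sample size on a change that is uncontrolled by design and does not estimate a between-arm difference. The direction of the error is clear if control patients improve at all: the future trial would be too small. Its size is conditional. Under the assumptions shown, a trial sized for 80% power has about 56%, 29% or 11% power if controls show 25%, 50% or 75% of the same change. The documents cannot narrow that range, because they give no EDEQ effect, SD, α, power or comparator for that trial. The firm conclusion is that the named input is wrong for its purpose, not that any particular power will result.

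**What to change.** Replace the sentence on the power analysis with:

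*The sample size of the future trial will be based on a justified minimum important between-group EDEQ difference, specified before the post-treatment data are released, with a sensitivity range. The within-group mean change or Cohen's d seen here will not be used as the assumed between-group effect. This study will supply the EDEQ SD (with its confidence interval, allowing for its imprecision), the baseline-to-post correlation, and attrition among all who start therapy.*

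Which confidence limit of the SD to use, and whether to allow for clustering, are optional choices for the team.

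The cost is rewording, taken through the article's amendment route where required, plus the work of justifying a target difference from sources outside this document. The study's data collection does not change, and the power analysis depends on end-of-study data, so there is time to correct it. The downside is that the projected future trial will probably be larger.
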